### Inclusion criteria

(1). Women aged between 18 and 35 years [36, 37](2). Diagnosed with PCOS using the Rotterdam criteria, which at least two of the following are present: oligo-ovulation or anovulation, clinical and/or biochemical signs of hyperandrogenism, and polycystic ovaries as defined by ultrasonography, which is presence of 12 or more follicles in each ovary measuring 2–9 mm in diameter, and/or increased ovarian volume (> 10 mL) [38](3). BMI ≥ 23 kg/m^2^.

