#### Study measurements

Prior and post to intervention, the following will be measured. Transvaginal ultrasound scan will be performed during the early follicular phase (cycle days 3–5) to document ovary morphology, including antral follicle count and ovarian volume. Fasting blood will be taken for 2–5 days during spontaneous menstrual cycle to check biochemical profiles, including AMH, LH, FSH, T, E_2_, sex hormone binding globulin (SHBG), dehydroepiandrosterone sulfate (DHEA-S), fasting insulin (FINS), and fasting blood glucose (FBG) level. Free androgen index (FAI = T × 100/SHBG) and homeostasis model assessment of insulin resistance (HOMA-IR = FINS × FBG /22.5) will be calculated. All ultrasound and blood tests were performed at the medical laboratory of Yueyang Hospital. All participants will receive a menstrual diary to record menstrual bleedings, menstrual frequency which will be calculated by dividing the number of menstrual bleedings by 3 (ordinal variables: “0,” “1/3,” “2/3,” “1”). Anthropometric indicators including weight, height, and BMI will be measured.

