#### Outcome measurements

The primary outcome is serum AMH level. AMH is the best marker of the ovarian function; it could be noticed as a suitable hormonal marker of the ovarian follicular count and as a diagnostic marker for ovarian hyperandrogenism [44–46]. Therefore, we choose AMH as the primary outcome.

Secondary outcomes include:(1). Menstrual frequency.(2). Biochemical profile including FSH, LH, T, E_2_, SHBG, DHEA-S, FAI.(3). Antral follicle count and ovarian volume.(4). BMI(5). HOMA-IR

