### Statistical methods

The intention-to-treat principle will be used in the statistical analysis. We will use multiple imputation, based on 5 replications and a chained equation approach method in the R MI procedure, to account for missing data. Continuous variables will be presented by mean ± standard deviation. We will use the Kolmogorov–Smirnov test to see the normality and Levene test to see homogeneity of variance. Data transformations, such as logarithmic transformation or arcsine square root transformation, will be applied in cases of a non-normal distribution. Analysis of variance (ANOVA) will be used for comparing the differences between groups, and Bonferroni test will be applied if the difference is found to be significant. Paired *t*-test will be used for comparing the differences within groups. Differences between groups of the categorical data (menstrual frequency) will be compared by Kruskal–Wallis test, and Nemenyi test will be applied if the difference is found to be significant. A two-sided *P* value less than 0.05 will be considered significant.

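### The within-arm paired t-tests on follicle count and ovarian volume, which can also count towards entry, cannot separate treatment effect from regression to the mean and should be descriptive only

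*Protocol article*

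**What the plan says.** Inclusion criteria uses the Rotterdam definition, under "which at least two of the following are present: oligo-ovulation or anovulation, clinical and/or biochemical signs of hyperandrogenism", with polycystic ovaries on ultrasound as the third feature. That feature is met by "presence of 12 or more follicles in each ovary measuring 2–9 mm in diameter, and/or increased ovarian volume (> 10 mL".

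Outcome measurements states "The primary outcome is serum AMH level". Its secondary outcomes include "Antral follicle count and ovarian volume", and also testosterone and the free androgen index.

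Study measurements places the scans before and after the intervention: "Transvaginal ultrasound scan will be performed during the early follicular phase (cycle days 3–5) to document ovary morphology". It does not say whether the pre-intervention scan is the one on which a woman qualified.

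Statistical methods plans two kinds of test for continuous outcomes. Between arms: "Analysis of variance (ANOVA) will be used for comparing the differences between groups", followed by Bonferroni comparisons. Within arms: "Paired *t*-test will be used for comparing the differences within groups". One two-sided threshold of 0.05 covers both, and nothing marks the within-arm tests as descriptive.

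**The concern.** A woman can be admitted partly because a measured follicle count or ovarian volume was high (or a measured androgen, where hyperandrogenism is established biochemically). A value selected for being high contains, on average, some upward measurement error and cycle-to-cycle variation. If that value also serves as the baseline, the repeat will tend to be lower in every arm, treated or not. A paired t-test reads that fall as change. Any other influence that moves all arms over 12 weeks enters the same test in the same way.

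The design makes misreading easy. The comparator is active (an oral contraceptive) and there is no untreated arm. The Background ends with two aims: to look at the effect of *Yi Jin Jing* in PCOS, and to compare it with aerobic exercise. Only the paired test appears to speak to one arm in isolation. If superiority over the contraceptive is not shown, a significant within-arm fall is the obvious result to fall back on, and it would not be evidence of benefit.

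**Working it through.** The article gives no figure on this point, so there is none to reproduce. It also gives no repeatability, no distribution of ovarian volume and no prevalence of the three features; those below are assumptions.

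**Inputs**
- From the article: volume threshold 10 mL; entry on any two of three features; 25 evaluable women per arm (Sample size, taken as given here); two-sided 0.05.
- Assumed: volume among candidates with mean 9 to 11 mL and SD 3 to 3.5 mL; test-retest correlation r of 0.7 to 0.9; oligo-/anovulation in 70-90% and hyperandrogenism in 30-60% of candidates, features independent; no treatment effect.

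**Step 1. Upper bound: every woman enters on volume and the qualifying scan is the baseline.** Expected fall = (1 − r) × SD × φ(c)/(1 − Φ(c)), with c = (10 − mean)/SD.
- Mean 9, SD 3, r = 0.7: c = 0.333; 0.3 × 3 × (0.3774/0.3694) = 0.92 mL.
- Mean 10, SD 3, r = 0.8: c = 0; 0.2 × 3 × (0.3989/0.5) = 0.48 mL.
- Mean 11, SD 3.5, r = 0.9: c = −0.286; 0.1 × 3.5 × (0.3830/0.6125) = 0.22 mL.

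Simulating 25 women per arm over these settings, the paired t-test rejects in 11-52% of arms instead of 5%.

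**Step 2. The rule actually written: two of three.** Take 80% with oligo-/anovulation, 60% with hyperandrogenism, mean 10 and SD 3, so that half of candidates exceed 10 mL.
- Chance of entry with high volume: 1 − 0.2 × 0.4 = 0.92.
- Chance of entry without it: 0.8 × 0.6 = 0.48.
- Share of candidates enrolled: 0.5 × 0.92 + 0.5 × 0.48 = 0.70.
- Mean excess of the qualifying value: (0.92 − 0.48) × 0.3989/0.70 = 0.25 SD, against 0.3989/0.5 = 0.80 SD when all are selected. The rule keeps about 0.25/0.80 = 31% of the regression.
- Expected fall: 0.3 × 0.25 × 3 = 0.23 mL at r = 0.7, and 0.1 × 0.25 × 3 = 0.08 mL at r = 0.9.

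At these prevalences, across the assumed means, SDs and correlations, two-sided rejection is about 5.5-8%. Widening the prevalences to 70-90% and 30-60% gives about 5-15%. The upper end arises when hyperandrogenism is uncommon, because more women must then qualify on morphology; the most selective corner (mean 9 mL, r = 0.7, 70% and 30%) goes slightly above 15%. If 60% of women also meet the follicle-count alternative independently of volume, rejection on volume is about 4-6%, which is nominal.

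**Step 3. False falls across three arms.** Counting only significant falls (nominal 2.5% per arm), and with 50-70% of candidates above threshold, the wider prevalences give 4-14% per arm. The chance that at least one of three arms shows a fall is then 1 − 0.96³ ≈ 11% to 1 − 0.86³ ≈ 36%, against 1 − 0.975³ ≈ 7%.

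**Step 4. What is not affected.** With a separate baseline scan, the mean change is about 0 and a false fall appears in about 2.5% of arms. The between-arm ANOVA, on post-treatment values or on changes, rejects in 4.4-5.7% of null trials in every setting tried, because randomisation gives each arm the same expected regression.

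**The case against.** The strongest reply is that the randomised comparison already deals with this. The trial is a three-arm superiority trial, the Discussion states its hypothesis against the control group, and the ANOVA with Bonferroni follow-up is planned. No section says that efficacy will be concluded from a within-arm change. All of that stands, and it limits the point to how the paired tests are labelled and used.

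Three stronger readings might be inferred, and the article supports none of them.
- *That women qualify on high follicle count or volume as such.* Morphology is one of three features and is not required. A woman with oligo-/anovulation and hyperandrogenism enters whatever her scan shows, and volume is itself only an alternative to follicle count. For testosterone the link is looser still: hyperandrogenism may be clinical only, and no biochemical threshold is given.
- *That regression to the mean will produce an apparent improvement.* This needs the qualifying scan to be the baseline scan. The article does not say so, and some wording leans the other way: already diagnosed patients are recruited, partly through gynaecologists, and dedicated pre-intervention measurements on fixed cycle days are described. A condensed article's silence here is not itself an error.
- *That the main result is biased.* AMH is not an entry criterion and could be touched only indirectly, through its correlation with follicle count; the between-arm tests hold their level.

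It can also be said that within-arm tests are a poor basis for efficacy in any parallel trial. That is true. Here the tested measures can also decide entry, which adds a specific route to a false result.

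**Conclusion.** The point holds in a limited form. Paired tests at 0.05 are planned, without a descriptive label, on measures that can count towards entry, and they cannot separate treatment effect from regression to the mean or other time effects. The likely size is modest: about 5-15% two-sided rejection per arm against 5%. That range rests on the qualifying scan being the baseline, correlations of 0.7 to 0.9, and assumed, independent feature prevalences. With a separate baseline scan the regression component disappears, although other time effects remain. The figures of 11-52% apply only to an entry rule that the article does not have. Secondary outcomes and supplementary tests are at stake, not the primary between-arm comparison. It is worth correcting because the correction is cheap and closes off an invalid single-arm claim.

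**What to change.** In Statistical methods, state that effectiveness is concluded only from between-arm contrasts. Replace the paired t-tests with mean within-arm changes and confidence intervals, labelled descriptive and not used for any claim. Adjusting the between-arm analysis for baseline would not by itself cure the paired tests, so this wording is needed in either case.

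In Study measurements, say which scan and hormone results serve as baseline. Where a diagnostic result pre-dates the baseline visit, use it for eligibility and let only the scheduled baseline measurement serve as the pre-treatment value. Trial status expects recruitment to finish in October 2021. If it is complete, this part reduces to reporting which measurement was used, while the change to the analysis wording can still be made before the data are analysed.

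The cost is wording only, with no added procedures. The downside is that the within-arm P values are lost.

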### Exclusion criteria

(1). Known disorders that mimic the PCOS, such as congenital adrenal hyperplasia, androgen-secreting tumors, and Cushing’s syndrome [38](2). Cardiovascular diseases and thrombotic diseases.(3). Acute or chronic hepatitis or nephritis.(4). Taking medications known to affect ovarian function within the past 3 months.(5). Any pulmonary or musculoskeletal diseases that could be impaired by exercise.(6). Participating or having regular exercise training during the past 3 months.(7). Patients suffer from mental problems.

### Interventions

Aerobic exercise intervention will be conducted on stationary bikes (Lode Excalibur Sport Lode, BV, Groningen, The Netherlands), for 50 min with an intensity level of 65–75% maximum heart rate, 3 times a week (one exercise session for every 2 days), accumulating to 150 min every week [14, 39, 40]. The sessions will include 5-min warm-up and cool down protocols before and after exercise. The 5-min warm-up protocol consists of joint movement, leg stretching, and step movements. The 5-min cool down protocol include walking slowly and stretching the major muscle groups of the body. Aerobic exercise will be conducted at Shanghai University of Sports under the supervision of an accredited physical trainer.

*Yi Jin Jing* group will conduct the *Yi Jin Jing* practice 30 min, 5 times a week [34]; the sessions will also include 5-min warm-up and cool down protocols before and after *Yi Jin Jing* practice. Practice will be conducted at Shanghai University of Sport with the guidance of an experienced *Yi Jin Jing* instructor who has been teaching *Yi Jin Jing* for 5 years.

Control group will take OCPs after randomization. OCPs are the first-line pharmacologic therapy for patients with polycystic ovary syndrome who are not trying to conceive [41, 42]. Diane-35, a kind of OCPs containing 2-mg cyproterone acetate and 35-μg ethinyl estradiol, is the first choice for the management of PCOS patients not seeking fertility in China [43]. The control group will take Diane-35 once daily at the same time from the 5th day of menstruation or withdrawal bleeding for a period of 21 days and for 3 menstrual cycles.

The study flow chart is shown in Fig. 1. We provide the control group with general exercise recommendations. For ethical reasons, we also provide them with videos of the aerobic exercise and *Yi Jin Jing*. Since exercise in the control group was not monitored, it was assumed that subjects in the control group would have no additional physical activity.

**Fig. 1 Fig1:**
[figure not shown]
Study flow chart

#### Adverse events

If serious injuries occur in the aerobic exercise group or the *Yi Jin Jing* group, such as a severe joint injury that makes it impossible to continue aerobic exercise or *Yi Jin Jing* intervention, it should be reported as an adverse event, and these subjects will stop aerobic exercise or *Yi Jin Jing* intervention and receive the usual medication, which is taking Diane-35. In case of adverse events, the study will have its own physical trainers and specialized practitioners to ensure proper measures are taken in cases of adverse events. Monitoring of adverse events for the aerobic exercise and *Yi Jin Jing* during the trial will include acute pain and heart rate. Therefore, adverse events occurring are estimated to be low.

Side effects of taking Diane-35 including headaches, nausea, weight gain, breast tenderness, and loss of libido will be monitored. If side effects occur, the drug should be stopped immediately for observation and the timing of continued use should be determined by the doctor. Serious adverse reactions will be reported to the ethical committee and other reactions that are thought to be causally associated with the intervention will be managed and recorded in the study.

If a subject suffers a sports injury, such as an ankle injury or muscle strain, during aerobic exercise or *Yi Jin Jing* training, the investigator will manage the acute phase of the sports injury according to the “PRICE” principle. PRICE stands for Protect, Rest, Ice, Compression, and Elevation. After the 48-h acute period, the investigator will provide the subject with appropriate free physiotherapy, such as muscle strength training and functional training. For the control subjects taking oral contraceptives, any side effects of the pill will be adjusted by the doctor and the cost of the examination and medication will be borne by the subject. Exercise and dietary advice and education will continue to be provided to all subjects after the 12-week study.

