#### Adherence and compliance

Prior to allocation, all participants will undergo a face-to-face education program with a doctor. All patients are assigned to smart phone app support. These steps are taken to ensure adherence. Control group patients will be asked to send monthly self-monitored information regarding their medication usage and any side effect via their phones for 3 months. Adherence and compliance will be determined from supervised exercise session attendance. Data from participants with less than 75% adherence will be included in the intention to treat analysis.

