## Discussion

Existing pharmaceutical agents such as OCPs have been associated with side effects, and OCPs may potentially have an adverse cardiovascular risk, elevated inflammatory markers, and decreased insulin sensitivity [48]. Non-pharmacological interventions, such as aerobic exercise and *Yi Jin Jing*, have limited side effects and are widely applicable. *Yi Jin Jing* is a pleasant mind–body exercise, which is similar to other TCEs, such as Tai Chi, which has mild intensity [49]. We hypothesize that *Yi Jin Jing* and aerobic exercise could decrease AMH level and improve menstrual pattern as well as other secondary outcomes compared to control group, thus improving ovarian function of young overweight/obese women with PCOS. Obesity, insulin resistance, and metabolic disturbances are predominant in older women with PCOS; the early management of younger PCOS women might reduce their risk of insulin resistance and metabolic disturbances later in life [7]. As a result, *Yi Jin Jing* may offer an easy and inexpensive alternative management for younger women with PCOS, to further avoid long-term complications.

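### Non-specific side effects are actively sought in the contraceptive arm only, so their counts cannot be compared between arms or used to support the claim that exercise has limited side effects

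*Protocol article*

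**What the plan says.** **Contraceptive arm.** The Adverse events section gives a list of general symptoms: "Side effects of taking Diane-35 including headaches, nausea, weight gain, breast tenderness, and loss of libido will be monitored". The Adherence and compliance section adds a schedule, for three months and for this arm only: "Control group patients will be asked to send monthly self-monitored information regarding their medication usage and any side effect via their phones".

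**Exercise arms.** The Adverse events section says that serious injuries should be reported as adverse events, with the example "such as a severe joint injury that makes it impossible to continue aerobic exercise" or *Yi Jin Jing*. Monitoring "during the trial will include acute pain and heart rate. Therefore, adverse events occurring are estimated to be low". Lesser injuries have a management paragraph that begins "If a subject suffers a sports injury, such as an ankle injury or muscle strain, during aerobic exercise". It describes treatment but does not say that these injuries are recorded as adverse events.

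**No arm named.** The same section states that "other reactions that are thought to be causally associated with the intervention will be managed and recorded in the study".

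**Use of the contrast.** The Discussion opens with the side effects of oral contraceptives. It then says that non-pharmacological interventions such as the two exercise programmes "have limited side effects and are widely applicable", and later offers *Yi Jin Jing* as an alternative way to manage the condition.

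**Blinding.** Participants, the exercise supervisor and the *Yi Jin Jing* instructor know the allocation.

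**The concern.** An event count reflects both how often events occur and how hard one looks for them. Here the looking depends on the arm in what is asked, how often, and what must be true before something is recorded. Headache and nausea are common complaints in people who take no drug. A control with a headache is prompted each month to report it. An exerciser with the same headache has no stated prompt, and it is recorded only if someone attributes it to the exercise. In an unblinded trial a headache is more readily attributed to a pill than to cycling or stretching, so the causality condition does not restore balance.

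What is at stake is the safety half of the argument for exercise. If the final report sets recorded side effects side by side, part or all of any difference in general symptoms could come from ascertainment, in the direction that the Discussion already expects.

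A second fault is one of logic. The Adverse events section infers from the scope of monitoring that few events will occur. What is monitored says nothing about how often harms happen. Narrow monitoring lowers only the number recorded.

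**Working it through.** The documents give no figure for harms, so there is none to reproduce. The check is a comparison of the text by arm, followed by an illustration.

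**Step 1. Collection as stated**

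| | Contraceptive arm | Exercise arms |
|---|---|---|
| General symptoms named | Five (headaches, nausea, weight gain, breast tenderness, loss of libido) | None |
| Periodic self-report | Monthly, any side effect | None stated |
| Monitoring | The named symptoms | Includes acute pain and heart rate |
| Stated reporting threshold | Any side effect | Serious injury |
| Other reactions | Recorded if thought causally related | Same clause |
| Staff contact at sessions | None stated | 3 × 12 = 36 (aerobic) or 5 × 12 = 60 (*Yi Jin Jing*) |
| Weight and BMI | Measured before and after | Measured before and after |

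The clear imbalance is in non-specific symptoms other than weight. For pain and injury, the last rows and the injury provisions point towards better capture in the exercise arms.

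**Step 2. Illustration**

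Inputs: 30 women per arm (Sample size section), so 30 controls against 60 exercisers pooled. Everything else is assumed: the same true rate *p* of non-specific symptoms in every arm, a share of 90% recorded in controls, and a smaller share in exercisers.

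Recorded proportions: π₁ = 0.9*p* in controls and π₂ = *s*·*p* in exercisers.

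Chance of a two-sided 5% result showing more in controls (normal approximation):

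Φ{[(π₁ − π₂) − 1.96·SE₀] / SE₁}, where
- SE₀ = √[π̄(1 − π̄)(1/30 + 1/60)], with π̄ = (30π₁ + 60π₂)/90
- SE₁ = √[π₁(1 − π₁)/30 + π₂(1 − π₂)/60]

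Worked case, *p* = 0.30 and *s* = 0.30:
- π₁ = 0.27 and π₂ = 0.09, or 8.1 versus 2.7 per 30
- π̄ = (8.1 + 5.4)/90 = 0.15
- SE₀ = √(0.15 × 0.85 × 0.05) = 0.0798
- SE₁ = √(0.27 × 0.73/30 + 0.09 × 0.91/60) = 0.0891
- (0.18 − 1.96 × 0.0798)/0.0891 = 0.26, and Φ(0.26) ≈ 0.60

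| Share recorded in exercisers | Recorded per 30 at *p* = 30%, control vs exercise | Chance of a false difference at *p* = 30% | Range for *p* = 20% to 40% |
|---|---|---|---|
| 90% (equal) | 8.1 vs 8.1 | 2.5% | 2.5% |
| 50% | 8.1 vs 4.5 | 29% | 21–38% |
| 30% | 8.1 vs 2.7 | 60% | 44–75% |
| 10% | 8.1 vs 0.9 | 89% | 74–97% |

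The approximation is rough at these counts. It shows direction and order of size only.

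**The case against.** The case on the other side has real force.

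- **No harms comparison is planned.** Harms are not among the listed outcomes, and the Statistical methods section describes no test of them. The Discussion's remark is rationale, and the hypothesis there concerns AMH, menstrual pattern and the other secondary outcomes. This stands. A reader might infer that a finding of fewer side effects with exercise is built into the trial, but the documents do not set one up. The point is only that the data could not support such a finding.
- **The exercise arms are not confined to pain and heart rate.** The text says that monitoring will include these, which is not exhaustive, and the clause on causally related reactions names no arm. It would be wrong to read the protocol as recording no general symptoms in exercisers. Capture there is unprompted and depends on attribution, so it is likely lower, but it is not zero.
- **The bias need not always favour exercise.** Exercisers have 36 or 60 planned supervised contacts. Controls send three monthly messages and receive exercise videos, with no injury monitoring stated for them. Pain and injury may be better captured in the exercise arms.
- **Weight gain is not a gap.** It is on the control list, but weight and BMI are measured in everyone.
- **An extreme calculation proves little.** Full capture against none at a 20% background rate gives 6/30 versus 0/30, with Fisher p = 2·C(30,6)/C(60,6) = 0.024. At 10% it gives 3/30 versus 0/30, with p = 2·C(30,3)/C(60,3) = 0.24. Neither should be quoted as the size of the problem, because zero capture conflicts with the general recording clause.
- **An article condenses.** The case report forms are not shown and might hold a common harms page. That is possible, but the article itself states that the monthly request goes to controls, and that stated difference is what remains.

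**Conclusion.** The point holds in a limited form. As written, non-specific symptoms are actively sought in one unblinded arm and not in the other two. Counts of such symptoms are therefore not comparable between arms and cannot support the Discussion's contrast between contraceptives and exercise. The sentence predicting few events does not follow from the one before it.

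The size cannot be derived from the documents. Under the assumed true rates of 20% to 40% and the unequal capture shares in the illustration, the chance of a nominally significant false difference runs from about 21% to 97%, depending mainly on how much is missed in the exercise arms. The conclusion about comparability needs only that capture be unequal, not any particular value.

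The primary AMH analysis is not touched. Nor is any comparison of weight or BMI. This matters for safety reporting and is cheap to put right, but it is not a threat to the main result.

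**What to change.** 1. Ask all three arms the same question about side effects and injuries, by phone, on the monthly schedule now used for controls. Name the same symptoms in every arm.
2. Record events under one definition in all arms, whatever their severity or presumed cause. Keep the causality judgement as a separate field.
3. Report the share of women with any event in each arm, with a confidence interval. These will be wide: at 27% of 30 women the half-width is 1.96 × √(0.27 × 0.73/30) ≈ 16 percentage points.
4. For participants already past the point of change, disclose that ascertainment differed by arm and make no between-arm harms comparison. The Trial status section puts recruitment from July 2019 to an expected end in October 2021, so this fallback may apply to many of them.
5. Delete the sentence inferring that adverse events will be low.

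**Cost.** A few extra questions for about 60 women. The app given to all participants is described only as adherence support, so using it to collect reports would be an addition; phone messages like those already asked of controls would do. The recorded event count in the exercise arms will rise. A change part-way through recruitment also means that ascertainment differs between earlier and later participants, which the report must state.

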## Blinding

Due to the characteristic of exercise intervention, all participants and the aerobic exercise supervisor and *Yi Jin Jing* instructor will not be blinded. But the staff who undertake outcome measuring and statistician who undertakes data processing will be blinded to group allocation.

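### The general rule for recording adverse events depends on judged causality, ethics reporting is worded only for serious reactions, and no general all-cause route is stated

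*Protocol article*

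**What the plan says.** The general rule is one sentence in the protocol article, Adverse events, with two limbs. The first is "Serious adverse reactions will be reported to the ethical committee". The second is that "other reactions that are thought to be causally associated with the intervention will be managed and recorded in the study".

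The same section has some narrower provisions:

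- For the two exercise arms it opens with "If serious injuries occur in the aerobic exercise group or the" Yi Jin Jing group, and says of such an injury that "it should be reported as an adverse event". No causality test is attached.
- Monitoring in the exercise arms "during the trial will include acute pain and heart rate".
- In the Diane-35 arm, side effects including "headaches, nausea, weight gain, breast tenderness, and loss of libido will be monitored".
- A later paragraph says how lesser sports injuries are to be managed, but not whether they are recorded.

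Under Adherence and compliance, control patients report their medication use and any side effects monthly by phone for three months. Under Blinding, the participants, the exercise supervisor and the Yi Jin Jing instructor "will not be blinded".

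**The concern.** Randomisation allows events to be compared between arms without deciding what caused any one of them. A rule that records an event only after someone has judged it related gives up that advantage, because the judgement comes before the data. Here those closest to the participants know the arm: the trainer and instructor by the Blinding section, and the doctor managing the pill by necessity. Blinded outcome assessors and a blinded statistician cannot restore an event that was never written down.

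The article also states its expectations. The Adverse events section expects few events with exercise. The Discussion associates oral contraceptives with side effects and says that non-drug interventions "have limited side effects and are widely applicable". A headache in a woman on Diane-35 matches a symptom already listed as a side effect. The same headache in a woman who exercises is easily judged unrelated. At stake are oversight of serious events and the fairness of any account of harms by arm.

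**Working it through.** The plan gives no figure on this point, so there is none to reproduce. The check is of wording, route by route.

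| Type of event | Stated provision | Causality condition |
|---|---|---|
| Serious injury, exercise arms | Reported as an adverse event | None |
| Acute pain, heart rate, exercise arms | Monitored | None |
| Named symptoms, Diane-35 arm | Monitored | Framed as side effects of the drug |
| Monthly phone report, control arm | Medication use and side effects | Framed as side effects of the drug |
| Serious adverse reaction | Reported to the ethics committee | Implied by the word reaction |
| Other reaction | Managed and recorded | Explicit |

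Two kinds of event have no stated route.

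1. A serious event that is not an injury and is judged unrelated, for example a hospital admission for another illness. It is not clearly a reaction, so reporting to the ethics committee is not clearly required. In the Diane-35 arm the injury route does not apply either, so an injury judged unrelated is in the same position.
2. A non-serious event judged unrelated, outside acute pain and heart rate in the exercise arms. The recording limb does not require it to be kept.

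The provisions also differ by arm. Drug side effects are monitored and asked for monthly in the control arm; pain, heart rate and serious injury are covered in the exercise arms. No symptom list is common to all three.

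The possible size can only be illustrated. Let p be the true rate of a symptom, the same in two arms, and let a1 and a2 be the proportions attributed to the intervention in each. If only attributed events are recorded:

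recorded difference = p × a1 − p × a2 = p × (a1 − a2)

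The values below are assumptions; none comes from the documents.

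| p | a1 | a2 | Recorded rates | Spurious difference |
|---|---|---|---|---|
| 20% | 90% | 10% | 18% v 2% | 16 points |
| 20% | 70% | 30% | 14% v 6% | 8 points |
| 20% | 50% | 50% | 10% v 10% | 0 |
| 10% | 90% | 10% | 9% v 1% | 8 points |

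The first row with 30 women per arm means 0.20 × 30 = 6 true events in each arm, of which 6 × 0.90 = 5.4 and 6 × 0.10 = 0.6 would be expected on record. Only the direction is general: at equal true rates, unequal attribution produces a difference in recorded harms, and equal attribution produces none.

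**The case against.** The strongest reply is that this is loose wording in a condensed article. The section moves between adverse events, side effects, adverse reactions and reactions without defining them. The explicit causality qualifier belongs to the second limb only. The sentence closes the paragraph on Diane-35, so its reach over all three arms is a reading and is not stated. The article does not say who judges causality. The case report form and full protocol, where detailed procedures usually stand, are not shown.

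Much of this stands, and it rules out several stronger readings that a reader might infer:

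- That nothing is recorded unless thought to be caused by the intervention. The serious-injury provision and the monitoring of acute pain and heart rate contradict this.
- That serious unrelated events are certainly withheld from the ethics committee. This rests on one undefined word; the text supports only that they may not be reported.
- That unrelated events disappear. Nothing says that they are discarded, and a form not shown might capture them.
- That a planned harms comparison is biased. Outcome measurements lists no safety outcome and Statistical methods plans no such comparison. The Discussion's remark on side effects is background rationale.
- That the small arms prove the point. An upper bound for zero events in 30 women reflects sample size under any recording rule and does not measure the effect of a causality filter.

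The reply does not remove the core. The article does not simply leave the recording rule to another document: it states one, and that rule carries a causality condition. If the actual form captures all events, the section misdescribes the trial and still needs correcting.

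**Conclusion.** The point holds in limited form. As written, the general recording rule for non-serious events depends on judged causality, and ethics reporting is worded only for serious reactions. Outside serious injuries, acute pain and heart rate in the exercise arms, no route is stated for events whatever their cause. Any description of harms by arm would therefore rest on attribution by people who know the arm.

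This assumes that the sentence is meant as the general rule for all three arms and that staff follow it literally. It also assumes that the judgement falls to those in contact with participants, which is likely but not stated. The size cannot be derived from the documents; the 18% against 2% example is illustrative only. AMH and the listed secondary outcomes are untouched. The change should be made because it concerns participant protection and an even-handed account of harms.

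**What to change.** Revise the Adverse events section to state that:

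1. all adverse events are recorded in the same way in all three arms, regardless of suspected cause;
2. seriousness, severity and relatedness are separate fields on the case report form, so that relatedness describes an event and does not decide whether it is kept;
3. all serious adverse events are reported to the ethics committee regardless of attribution;
4. any summary of harms by arm uses all events, with related events listed secondarily.

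One term for each concept, used throughout the section, would remove the doubt over reactions and events.

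The cost is protocol and form wording and a few more entries per participant, with no added visits and no change to any treatment rule. The limit is timing: under Trial status, recruitment began in July 2019 and was expected to finish in October 2021. Events not recorded before the change cannot be fully recovered, and this should be stated when harms are reported.
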